**Outcomes**			
	1 item of the PTPQ^b^ [61]	Satisfaction with the quality of information received about prognosis and treatment	
	EORTC QLQ-INFO25^c^ information about the disease, medical tests, and treatments scales (items 31-43) and satisfaction with information items (52-55) [60]	Perception of information received about the disease, medical tests, and treatments Satisfaction with information	
	SCNS-SF34^d^, Psychological (items 6-14 and 17) and Care and Support needs (items 18-22) [85]	Perception of unmet psychological (eg, anxiety, fear of cancer spreading, and uncertainty) and care and support needs (eg, reassurance and sensitivity to feelings and emotional needs)	
**Correlates**			
	12 items of the PTPQ [61]	Beliefs regarding the likelihood of cure, the importance and helpfulness of knowing about prognosis, and the primary goal of cancer care Preference for information about treatment	
	HADS^e^ [86]	Anxiety and depression	
	Brief COPE^f^ [87]	Coping strategies	

^a^QPL: question prompt list.

^b^PTPQ: Prognosis and Treatment Perceptions Questionnaire.

^c^EORTC QLQ-INFO25: European Organization for Research and Treatment of Cancer Quality of Life Questionnaire–Information Module.

^d^SCNS-SF34: Supportive Care Needs Survey–Short Form.

^e^HADS: Hospital Anxiety and Depression Scale.

^f^COPE: Coping Orientation to Problems Experienced.

Patients’ perception of prognosis and treatment will be assessed using the Prognosis and Treatment Perception Questionnaire (PTPQ) [61]. The PTPQ assesses beliefs regarding (1) the likelihood of cure, (2) the importance and helpfulness of knowing about prognosis, (3) the primary goal of cancer care, (4) preference for information about treatment, and (5) satisfaction with the quality of information received about prognosis and treatment (Table 3). This questionnaire has been translated into French and pilot-tested according to the European Organization for Research and Treatment of Cancer Quality of Life Group guidelines [88].

The perception of information received about the disease, medical tests and treatments, and satisfaction with overall medical information will be measured by the European Organization for Research and Treatment of Cancer Quality of Life Questionnaire–Information Module (EORTC QLQ-INFO25) scale [60]. The perception of unmet psychological (eg, anxiety, fear of cancer spreading, and uncertainty) and care and support needs (eg, reassurance, sensitivity to patients’ feelings, and emotional needs) will be measured by the Supportive Care Needs Survey–Short Form (SCNS-SF34) [85].

Additional patient information will include coping strategies (usual strategies when facing stressful life events) and distress (during the past week), as measured by the Brief Coping Orientation to Problems Experienced [87] and the Hospital Anxiety and Depression Scale [86] questionnaires, respectively.

Questionnaires will be completed within 2 weeks of the consultation; if not completed within this time-lapse, 1 reminder will be made by telephone. Questionnaires not returned after 1 month will be considered missing.

As indicated in Table 2, a sample size of 80 patients (40 patients by tumor site) is planned. Sample sizes up to 40 per group are expected to provide estimates that are precise enough to assess the feasibility of QPL use and obtain preliminary clinical data for further randomized controlled trials of this tool [89].

#### Step 1c: Content and Implementation of the QPL in Routine Practice

From steps 1a and 1b, a core QPL comprising issues (ie, questions and concerns) commonly expressed by patients with resistant cancer, complemented by specific issues for either MBC or MUM cancer sites, will be developed. Issues to compose this QPL will be selected based on descriptive analyses of patients’ responses to relevant items of the PTPQ, EORTC QLQ-INFO25, and SNCS-SF34 questionnaires. For example, if ≥50% of patients report that they received little or no information about the spread of their illness from the EORTC QLQ-INFO25 and are dissatisfied with the information provided, this issue will be prioritized while composing the QPL. Other issues will be similarly selected based on responses to items of the SCNS-SF34 (50% of patients reporting medium or high unmet needs) or the PTPQ (50% reporting that the quality of information on treatment options received from the oncologist was fair or poor). These quantitative data will be considered in conjunction with the qualitative interview data. A thematic content analysis will help identify issues that patients would like to address more frequently during oncology consultations dealing with cancer resistance.

Focus groups will be implemented to discuss the provisional QPL. On the basis of research on sample size calculation for the content analysis of qualitative interviews [83], we aim to conduct 2 focus groups of approximately 8 different participants each (patients with any type of metastatic cancer, oncologists, supportive care specialists, and cancer care administrators from various oncology centers or departments in France), approached through snowball purposive sampling. Participants will be identified from contacts of *expert* patients (patient university, Institut Curie *Site de Recherche Intégrée sur le Cancer* patient and partner representatives, and cancer patient associations) and oncology professionals (UNICANCER oncology professionals’ network and French Association for Supportive Care—Association Francophone pour Soins Oncologiques de Support).

The group interview guide will address the following two central themes: (1) the appropriateness (adequacy, relevance, and importance for treatment resistance in oncology generally and in triple-negative and luminal B MBC and MUM specifically) and acceptability (satisfaction, anxiety-provoking, intrusiveness, irrelevance, and incompleteness) of the QPL content (questions, concerns or emotions, and narratives or testimonies), structure (logical order, length, and complexity), and format (paper, website, and app) and (2) the feasibility (obstacles and facilitating strategies such as complementary coaching, formal implementation blueprint, educational materials, and audit and feedback [90]) and optimal circumstances and procedures (when: timing of provision or access; where: hospital or home; how: text or video; who: coach or health educator expertise) for implementing the QPL in real-world clinical practice and ensuring its adoption and sustainability. The internationally designed QPL for patients with advanced cancer has been revised and further developed for the cancer resistance context by keeping, removing, or adding items according to their relevance and importance generally for treatment resistance in oncology and specifically for triple-negative and luminal B MBC and MUM.

Each focus group will be conducted via Microsoft Teams videoconference to facilitate participation and will last an estimated 90 to 120 minutes.

#### Step 1d: Content Validation With the Delphi Process

To facilitate the collection of individuals’ feedback on the provisional QPL version, a 2-round web-based Delphi process [91] will be performed involving participants through snowball purposive sampling. Participants in the focus groups will be offered the opportunity to participate in the consensus method. Other eligible participants (see criteria in Textbox 1) will be solicited according to the same recruitment methodology as for the focus groups.

The Delphi survey assesses (1) each QPL item (instructions, questions, concerns or emotions, and narratives or testimonies) in terms of content appropriateness, formulation clarity, structure, format, and acceptability on a 5-point Likert agreement scale and (2) the feasibility of a complementary coaching intervention and implementation guidance.

The procedure comprises successive evaluations according to the following steps:

Participants will indicate their level of agreement on the relevance and clarity of each proposed item of the QPL (ie, instruction sentences and questions or concerns) and implementation guidance (ie, ideas or sentences) using a 5-point Likert scale (ranging from 1=*strongly disagree* to 5=*strongly agree*). The overall length and clarity of the tool and guidance will also be assessed.Participants will comment and propose changes or additions to the QPL and guidance if required based on the following questions addressed to patients (professionals):

What would you (your patients) have liked to ask?

What questions do you (your patients) often not ask, that you (I) wish you (they) would ask?

The research team will analyze the data obtained. It will then identify the issues on which there is consensus and make possible modifications and additions based on the participants’ comments.Following the first evaluation, the modified items will be submitted to a second evaluation by participants who will be invited to rate each question, concern, or sentence on a 5-point Likert scale, and responses will be rated as *essential* or *important*; validation will be determined by an a priori threshold of ≥4.0.Following the second evaluation, QPL version 1 and guidance will be validated in its final version.

A total of 2 rounds of Delphi surveys administered via REDCap (Research Electronic Data Capture; Vanderbilt University) software will be performed, including 30 participants responding to the first survey on a first QPL version and then the second survey on a QPL version revised from the initial survey responses and comments.

### Step 2: QPL and Implementation Pilot Testing

The second step of the study pilot tests the QPL version 1 for its acceptability, feasibility, potential clinical utility, and sustainability. Consecutive patients (n=80) responding to the same eligibility criteria as in step 1b will be recruited. They will receive the QPL version 1 to prepare their subsequent oncology consultations, either a consultation during which the diagnosis of cancer resistance is communicated or in the course of a new disease-targeted treatment follow-up consultation. They will be invited to complete the same standardized questionnaires as in step 1b.

Additional questions will address the QPL acceptability in terms of uptake (the QPL has been read before the consultation), use (QPL items have been raised during the consultation), and patients’ and clinicians’ perceived helpfulness and satisfaction with this tool and its use in clinical practice.

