### Clinical Setting

The QPL will be developed in the following two clinical contexts, which are prone to cancer resistance, and contrasted in terms of epidemiology, life expectancy, long-term treatment options, and expected effectiveness: (1) triple-negative and luminal B metastatic breast cancer (MBC) and (2) metastatic uveal melanoma (MUM), both within the first 3 lines of anticancer treatment after treatment resistance has occurred.

Triple-negative and luminal B MBC represents approximately 15% and 50% of all breast cancer cases, respectively [67], and recurs with distant metastasis in approximately 30% of early-stage patients [68]. MBC is an incurable disease, with a median overall survival of 3 years and a 5-year survival rate of 25% [69]. Patients with MBC are generally followed by their oncologist for years, punctuated by occurrences of treatment resistance for which a new treatment regimen may be offered. This implies successive disclosures of the progressing disease and discussions of alternative treatment regimens [70].

Uveal melanoma is a rare cancer [71]. Up to 50% of patients with uveal melanoma develop metastases, mostly in the liver, within a median time of 2 to 3 years [72]. Once metastasis occurs, the median overall survival ranges from 9 to 12 months because of the lack of effective treatment options [73]. Most patients with MUM are referred to a medical oncologist after a multidisciplinary tumor board meeting. Medical oncologists then inform patients about metastatic progression and possible treatment alternatives. The dismal prognosis and rapid evolution of the disease are challenging aspects in the communication between oncologists and patients. A discrepancy in knowledge appears when the medical oncologist is aware of the patient’s poor prognosis while the patient is still in good shape and does not expect such quick, fatal outcomes.

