**Figure 1 figure1:**
[figure not shown]
Sequential study design. MBC: metastatic breast cancer; MUM: metastatic uveal melanoma; QPL: question prompt list.

**Table 1 table1:** Sequential collaborative mixed methods approach.

Steps		Aim	Method	Sources or population
**Step 1: QPL^a^ development**		To develop a QPL for the treatment of resistant cancer in 2 contrasting clinical contexts: MBC^b^ (triple-negative and luminal B) and MUM^c^	Mixed methods	Professionals and patients
	Step 1a	To explore oncologist-patient communication issues (ie, difficulties, obstacles, and strategies) in the context of cancer resistance	Individual interviews	Professionals, that is, oncology physicians, supportive care specialists, and laboratory researchers (from bench to bedside)
	Step 1b	To explore communication difficulties and information and support needs that are experienced by patients with resistant cancer after an oncology consultation to initiate or follow a new disease-specific treatment after cancer resistance has developed	Standardized questionnaires Individual interviews	Patients with MBC (triple-negative and luminal B) or MUM within the first 3 lines after first cancer resistance^d^
	Step 1c	To revise the content of a QPL developed for patients with advanced cancer and elaborate an acceptable and feasible clinical implementation, potentially facilitated by a coaching intervention	Focus groups	Professionals and patients (any type of metastatic cancer)
	Step 1d	To validate the content of a QPL preliminary version adapted to cancer resistance and the MBC (triple-negative and luminal B) and MUM contexts (version 1) and the implementation guidelines	Delphi surveys	Professionals and patients (any type of metastatic cancer)
Step 2: QPL pilot testing		To pilot-test a QPL version 1: acceptability, feasibility, and potential clinical utility (effects)	Standardized questionnaires (same as in step 1b)	Patients with MBC (triple-negative and luminal B) or MUM within the first 3 lines after first cancer resistance

^a^QPL: question prompt list.

^b^MBC: metastatic breast cancer.

^c^MUM: metastatic uveal melanoma.

^d^Patients in step 1b comprise a historical control group to which the patients provided with the preliminary question prompt list in step 2 will be contrasted.

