#### Step 1b: Patients’ Communication Experience and Information and Support Needs in the Oncology Consultation Dealing With Treatment Resistance

##### Overview

A cross-sectional assessment of patients’ communication needs in the context of cancer resistance will then be performed. Patient enrollment started in January 2021 and will take place over 1 year.

Consecutive patients will be identified via lists of oncology consultation agendas in an oncology center (Institut Curie, Paris). If they respond to the inclusion and exclusion criteria listed in Textbox 1, they will be invited to participate in the study.

Patients’ sociodemographic data (age, gender, educational level, and marital, parental, and professional status) and clinical data (date of initial diagnosis, disease recurrence and metastatic occurrence, stage, previous and current disease-targeted treatments, and supportive care interventions) will be collected from patients or medical records to describe the study population.

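### Step 1b, step 2 and the shared eligibility criteria define the eligible consultation inconsistently, so the mix of visit types may differ between the historical control and QPL groups

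*Protocol article*

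**What the plan says.** Step 2 states its eligibility by reference to step 1b: "Consecutive patients (n=80) responding to the same eligibility criteria as in step 1b will be recruited". In Textbox 1 those criteria require that the patient has been told of the cancer diagnosis and of the resistance to treatment.

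Step 2 then sets the order of events: "They will receive the QPL version 1 to prepare their subsequent oncology consultations". It names the visit concerned as "either a consultation during which the diagnosis of cancer resistance is communicated or in the course of a new disease-targeted treatment follow-up consultation".

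For step 1b, Table 1 describes patients assessed "after an oncology consultation to initiate or follow a new disease-specific treatment after cancer resistance has developed". The step 1b overview describes the sampling without naming a visit type: "Consecutive patients will be identified via lists of oncology consultation agendas in an oncology center". On timing, the step 1b quantitative section says: "Questionnaires will be completed within 2 weeks of the consultation". Step 2 uses the same questionnaires.

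Under Data Analysis (Quantitative Data), step 1b serves as the historical control for step 2. Similarity is expected because inclusion is consecutive in both steps, and it is to be checked on sociodemographic and clinical data. The outcomes are then compared by bivariate analysis.

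**The concern.** The outcomes are information received, satisfaction with it, and unmet psychological and support needs, all collected shortly after one index visit. What happens at that visit can plausibly move them. The article's own Background describes the news of resistance as a critical moment that provokes anxiety.

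If one group holds more disclosure visits than the other, the step 1b versus step 2 difference carries a visit-type effect as well as any QPL effect. This is the only comparison between a group with the QPL and a group without it, and nothing stated in the article would separate the two effects.

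The conflict with the eligibility rule has a second consequence. Read literally, the step 2 text allows a question list about cancer resistance to reach a patient who has not yet been told of it, while the criteria it invokes rule that out.

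**Working it through.** No stated figure is in dispute. The planned 80 per step is the sum of the two tumor sites (40 + 40 = 80). The check sets the passages side by side.

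**1. Eligibility against visit type in step 2.**
- Textbox 1, adopted by step 2: the patient is already informed of resistance at inclusion.
- Step 2: the QPL is handed over before the visit, so inclusion precedes the visit.
- Step 2: that visit may be the one at which resistance is communicated.

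For a first disclosure, the patient would have to be informed before being informed, so the rules conflict. For a later disclosure they can be reconciled: the Clinical Setting section says of metastatic breast cancer, "This implies successive disclosures of the progressing disease and discussions of alternative treatment regimens". A patient who knows of one resistance can be eligible before hearing of the next. The contradiction is therefore confined to first disclosures.

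**2. Visit types named in each step.**

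| Visit type | Step 1b (Table 1) | Step 2 |
|---|---|---|
| Resistance communicated | not named | named |
| New treatment initiated | named | not named |
| New treatment followed | named | named |

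Only follow-up appears in both.

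**3. Effect of timing.** Step 1b patients are surveyed after the visit, so someone told of resistance at an initiation visit may count as informed by then. Step 2 patients must be identified beforehand. The same criterion can thus filter differently in the two steps. Applied strictly, it would remove first disclosures from step 2 but might leave some in step 1b. Applied loosely, it could do the reverse. The direction of any imbalance is unknown.

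**4. Whether the planned check would see it.** The clinical data listed for step 1b are the dates of diagnosis, recurrence and metastasis, stage, previous and current treatments, and supportive care. Consultation type is not among them. A bivariate comparison of outcomes by step does not adjust for it.

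**5. Size.** Let p1 and p2 be the shares of disclosure visits in steps 1b and 2, and d the shift in outcome at such visits, in SD units. Then

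bias = (p2 − p1) × d.

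The documents give none of the three. For scale only, assume p1 = 0, p2 from 0.10 to 0.50, and d from 0.2 to 0.8:
- smallest: 0.10 × 0.2 = 0.02 SD
- largest: 0.50 × 0.8 = 0.40 SD
- if p1 = p2: zero

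The 95% confidence half-width at 80 versus 80 is about 1.96 × √(2/80) = 0.31 SD. The assumed range therefore runs from negligible to larger than the sampling error. It shows only that the bias cannot be bounded from the article.

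**The case against.** The strongest reply is that no difference between the groups has been shown. Step 2 does not speak of a first disclosure, and successive disclosures are described. A step 1b visit to initiate treatment may itself be the visit at which resistance is disclosed. The Table 1 entry states an aim and is not an exclusion, and the agenda sampling is unrestricted by visit type. All of this stands. A reader might infer that the control and QPL groups do differ by consultation type, or that the comparison has a known high false-positive rate. The documents support neither: the disclosure shares and the outcome shift would both have to be assumed.

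A reader might also infer that step 1b patients could re-enter in step 2 and contaminate the controls. The limitations paragraph says the two assessments do not follow the same individuals, and the control responses are used to build the QPL and so precede it. That point is not pursued.

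Two further replies carry weight. The article presents the comparison as limited, preliminary and preparatory to randomized trials, and acceptability and feasibility do not depend on it. And a full protocol may hold data fields that an article omits. The first lowers the severity. The second may mean that visit type is already captured, but it does not remove the conflict, because the article itself states both the eligibility rule and the two differing visit descriptions.

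**Conclusion.** The point holds as an inconsistency that creates a risk of bias, not as a demonstrated bias. Table 1, Textbox 1 and the step 2 text do not describe one eligible consultation. For first disclosures the step 2 text contradicts the criteria it adopts. For the other visits the two steps name different types, so the mix may differ between the groups, and the stated comparability check and unadjusted analysis would neither reveal nor correct it.

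The size and sign of any effect cannot be derived from the documents. The conclusion assumes only that outcomes collected within 2 weeks of a visit can depend on what was said at it. Severity is should-fix: the comparison is declared preliminary, but it is the study's only evidence on clinical utility against a group without the QPL.

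**What to change.** Before step 2 opens:

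- Reconcile Table 1, Textbox 1 and the step 2 text. Which patients receive the QPL, and when, is for the sponsor to settle; the text needs to give one answer.
- State one consultation definition for the step 1b versus step 2 clinical-utility comparison.
- Record consultation type prospectively in step 2, and recover it from medical records or consultation agendas for step 1b patients already surveyed.
- Stratify the comparison by consultation type, or restrict it to types present in both steps. Use any other step 2 visits for acceptability and feasibility only.

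The cost is a wording change, one data field in step 2, and retrospective capture for the controls. The Results section reports 39 + 28 = 67 questionnaires completed by October 31, 2021, so most of the 80 controls would need it. Some control visits may prove unclassifiable, and restriction may leave fewer patients in the comparison.
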